**CLINICAL PHARMACOLOGY**

1. Evaluation of the tolerance and pharmacokinetics of a single oral dose of ansofaxine hydrochloride extended-release tablet in healthy volunteers in a randomized, double-blind, placebo-controlled, dose-escalation study.

Seventy-two male and female healthy volunteers were enrolled in this trial, including 60 subjects receiving Ansofaxine Hydrochloride Extended release Tablet (study drug) orally and 12 subjects receiving placebo. 20 case-times of adverse events occurred in 14 subjects receiving study drug, and 9 case-times of adverse events were possibly related to the study drug, including 4 case-times of nausea, 1 case-time each of dizziness, weakness, diarrhea, supraventricular arrhythmia (unconfirmed) and sinus tachycardia. All the adverse events possibly related to the study drug were mild and spontaneously relieved without treatment. No clinically significant change related with the study drug was seen in physical examination, blood oxygen saturation and laboratory examination. The study results showed a good safety and tolerability for orally single dose of Ansofaxine Hydrochloride Extended release Tablet in the dose range of 20~200 mg.

At the orally single dose of 20, 40, 80, 120, 160 and 200 mg Ansofaxine Hydrochloride, Ansofaxine was rapidly metabolized to the active metabolite *O-*demetylvenlafaxin, a very low concentration of parent drug could be detected in individual plasma and urine samples in 80~200 mg dose group, the median T_max_ was 6.00~8.00 hours, t_1/2_was 8.30~11.29 hours, C_max_ and AUC were increased approximately in proportion to dose increase, as calculated by *O-*demetylvenlafaxin, and about 50% oral drug was excreted via kidney in a form of *O-*demetylvenlafaxin.

1. Evaluation of 2-period, 2 sequence an crossover,comparative pharmacokinetics study of ansofaxine hydrochloride extended-release tablet after fasting and after fed in healthy volunteers

Twelve healthy volunteers were enrolled in this trial, including half men and half women. A total of 5 case-times of adverse events occurred in 3 subjects, only one was possibly related with the study drug and appeared nausea, mild in intensity and spontaneously relieved without treatment. The study results showed a good safety and tolerability for orally single dose of Ansofaxine Hydrochloride Extended release Table 120mg under fasted state and after high-fat meal.

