## Exclusion criteria

1. Subjects who are allergic or known to be allergic to venlafaxine and desvenlafaxine
2. Subjects who have previously failed treatment with venlafaxine at an adequate dose for an adequate time, or patients who have refractory depression and have previously failed treatment with at least 2 types of antidepressants at an adequate dose for an adequate time;
3. Subjects who have greater than 25% change in HAM-D17 total score at baseline from screening visit;
4. Subjects who have clear suicide attempt or behavior with Suicide score in HAM-D17 ≥ 3 points;
5. Pregnant or breastfeeding women, or men and women of childbearing age who do not use a medically acceptable form of contraception or fail to continue contraception until 28 days after the last dose of the study medication;
6. Subjects with DSM-IV-TR axis I diagnoses other than MDD, who receive treatment for such diagnoses (including current or previous diagnoses of anorexia nervosa or bulimia nervosa), or who have been diagnosed with depressive neurosis within the past 2 years; Depressive episode secondary to other psychiatric disorder or somatic disease;
7. Subjects with MDD secondary to other organic or mental disorders;
8. Subjects with a history of seizures (except spasms caused by infantile hyperpyretic convulsions);
9. Subjects who have received electroconvulsive therapy (ECT) within 3 months prior to screening or need current ECT treatment per investigator’s judgment, have received systematic psychotherapy (interpersonal relationship therapy, dynamic therapy, cognitive behavioral therapy) within 3 months of screening, have received transcranial magnetic stimulation (TMS) 3 months prior to screening, or have received light therapy 2 weeks prior to screening;
10. Subjects who have regularly taken anti-depressants within 2 weeks prior to screening, or have withdrawn from psychotropic drugs for less than 7 half-lives (at least 2 weeks for monoamine oxidase inhibitors and at least 1 month for fluoxetine) before randomization/enrollment;
11. Subjects with a history of serious unstable cardiovascular, hepatic, renal, blood or endocrine diseases;
12. Subjects with hypertension whose blood pressure is poorly controlled (SBP≥140 mmHg or DBP≥90 mmHg at the screening and baseline visit);

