13. Subjects with a history of gastrointestinal diseases known to interfere with drug absorption or excretion, or those with a history of surgery that is known to interfere with drug absorption or excretion;
14. Subjects with a history of increased intraocular pressure or narrow angle glaucoma;
15. Subjects with clinically significant abnormal results as considered by the investigator shown by a physical examination, laboratory test or urine drug test (e.g., ALT or AST> 1.5 times the upper limit of normal; Creatinine clearance > the upper limit of normal; abnormal measurements of thyroid function which are of clinical significance);
16. Subjects with Electrocardiogram (ECG) abnormalities that are clinically significant at screening and baseline, and investigators believe that it is inappropriate for the subjects to be enrolled, such as QTc interval >450 ms for male and QTc interval >460 ms for female;
17. Subjects who have participated in clinical trials on other drugs within 3 months prior to screening;
18. Subjects with serious acute or chronic diseases, mental illnesses or clinically significant abnormalities as shown in laboratory tests, of which investigators believe that the subjects are not suitable for this study

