## Dose adjustment

Change the dosage is not allowed in the clinical trial. The subjects may be suspended if subjects experience adverse events and was agreed to by the investigator, the subjects will get other treatment based on inverstigator’s judgement.

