4. Laboratory examination: the complete blood cell count includes white blood cell count, lymphocyte count, neutrophil count, eosinophil count, basophil count, monocyte count, red blood cell count, hemoglobin, hematocrit, platelet count; routine urinalysis includes white blood cell, PH, nitrite, protein, glucose, ketone body, urobilinogen, bilirubin, red blood cell, specific gravity; serum chemistry includes alanine aminotransferase, aspartate aminotransferase, total protein, albumin, alkaline phosphatase, γ- glutamyl transpeptidase, total bilirubin, direct bilirubin, urea nitrogen, creatinine, uric acid, sodium, potassium, chlorine, calcium, phosphorus, total cholesterol, triglyceride, high-density lipoprotein cholesterol, low-density lipoprotein cholesterol, fasting blood glucose, lactate dehydrogenase, creatine kinase, creatine kinase isoenzyme; serology includes testosterone and prolactin.
5. It is applicable for the women of childbearing potential.
6. Urine drug screening test: morphine, methamphetamine, methadone, Phencyclidine, Tetrahydrocannabinolic acid, amphetamine, cocaine, Barbiturates, Benzodiazepines, tricyclic antidepressants.
7. Drugs in wash-out period: dispensed on Day -8 and used from Day -7.

Abbreviations: HAM-D_17_＝ Hamilton Depression Scale – 17; HAMA= Hamilton Anxiety Scale; CGI-S = Clinical Global Impression scale – severity; CGI-I = Clinical Global Impression scale – overall improvement; VAS-PI = Visual analogue scale - pain intensity; FT3 = free triiodothyronine; FT4 = free thyroxine; TSH = thyroid stimulating hormone; HbsAg = hepatitis B surface antigen; anti-HCV = hepatitis C antibody

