### Laboratory tests

1. Laboratory safety examinations will be performed at screening, visit 4 and 6 or end of the study, including:

- Complete blood cell count: white blood cell count, lymphocyte count, neutrophil count, eosinophil count, basophil count, monocyte count, red blood cell count, hemoglobin, hematocrit, and platelet count.
- Routine urinalysis: white blood cell, PH, nitrite, protein, glucose, ketone body, urobilinogen, bilirubin, red blood cell, specific gravity.
- Serum chemistry: alanine aminotransferase, aspartate aminotransferase, total protein, albumin, alkaline phosphatase, γ-glutamyl transpeptidase, total bilirubin, direct bilirubin, urea nitrogen, creatinine, uric acid, sodium, potassium, chlorine, calcium, phosphorus, total cholesterol, triglyceride, high-density lipoprotein cholesterol, low-density lipoprotein cholesterol, fasting blood glucose, lactate dehydrogenase, creatine kinase, creatine kinase isoenzyme.
- Serology: testosterone, prolactin.

1. Laboratory examination screening variable, only performed at screening, including:

- Free triiodothyronine, free thyroxine, thyroid-stimulating hormone
- Hepatitis B surface antigen and hepatitis C antibody
- Urine drug screening test: morphine, methamphetamine, methadone, Phencyclidine, Tetrahydrocannabinolic acid, amphetamine, cocaine, Barbiturates, Benzodiazepines, tricyclic antidepressants

1. Urine pregnancy test will be performed for women of childbearing potential at screening, baseline, visit 6 and end of treatment.

All the abnormal laboratory examination items of clinical significance will be re-measured after start dose of study drug, until they are recovered to normal, or baseline level, or stable. If the laboratory examination value is not recovered to normal, or baseline level or stable within a reasonable time limit, relevant reason should be found out and the sponsor will be informed.

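### Exclusion 15 gives its only renal laboratory example in the wrong direction: it flags high creatinine clearance, while impaired excretion lowers clearance

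*Protocol*

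**What the plan says.** Protocol section 5.2, item 15, excludes subjects with "clinically significant abnormal results as considered by the investigator" on physical examination, laboratory testing or urine drug testing. Three laboratory examples follow in parentheses, introduced by e.g.:

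- liver: ALT or AST above 1.5 times the upper limit of normal;
- kidney: "Creatinine clearance > the upper limit of normal";
- thyroid: clinically significant abnormal function, with no numeric limit.

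The Abstract repeats the item with the same renal wording.

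Two other exclusions bear on renal function. Item 11 covers a "history of serious unstable cardiovascular, hepatic, renal, blood or endocrine diseases". Item 18 covers "clinically significant abnormalities as shown in laboratory tests" where the investigator considers the subject unsuitable.

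The laboratory panel includes serum creatinine (section 7, flow chart note 4: "total bilirubin, direct bilirubin, urea nitrogen, creatinine, uric acid"; section 8.2.4: "urea nitrogen, creatinine, uric acid, sodium, potassium") and does not list creatinine clearance. Section 7.1 schedules this chemistry at screening.

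On elimination, the clinical pharmacology part of section 1 reports that "about 50% oral drug was excreted via kidney" in the form of the active metabolite, ODV. On dosing, section 6.5 says "Change the dosage is not allowed in the clinical trial", and then lets treatment be suspended for adverse events.

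**The concern.** Creatinine clearance measures how well the kidney excretes, and it falls as function worsens. An upper limit therefore points away from the patients whom a renal safety criterion is meant to find.

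The drug's main active moiety depends substantially on renal excretion, and the trial uses fixed doses up to 160 mg/day. Eligibility is where a renal check does most good. Under the flow chart, chemistry is drawn at screening, is not repeated at baseline, and is next drawn at visit 4 (day 14 ± 1). The only renal laboratory guide offered to sites at screening points the wrong way. What is at stake is the clarity of a safety criterion, not any statistical property of the trial.

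**Working it through.** The Protocol gives no figure to reproduce here. The check concerns the direction of an inequality and whether any other text corrects it.

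**1. Direction.** Creatinine clearance equals creatinine production divided by serum concentration. Assume constant production. If serum creatinine rises to m times a patient's normal value, clearance becomes 1/m of normal:

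- m = 1.33: 1/1.33 = 75%
- m = 1.5: 1/1.5 = 67%
- m = 2: 1/2 = 50%

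These multiples are illustrative and do not come from the Protocol. Each step towards worse excretion moves clearance further below the printed limit, so no degree of impairment can satisfy the example as written.

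**2. Comparison with the liver example.** For ALT and AST, above the limit means worse, so the greater-than sign is right. The renal example has the same form but uses a quantity for which higher does not mean worse excretion.

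**3. Is it corrected elsewhere?** The Abstract and section 5.2 carry the same phrase. Item 11 concerns history and gives no laboratory limit. Item 18 is a general clause, also without a renal limit. No other passage states a renal threshold.

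**4. What was probably meant.** Serum creatinine is in the panel and clearance is not. The List of Abbreviations defines Cr as creatinine and has no entry for clearance. A greater-than sign with an upper limit of normal suits a serum value. All three point to serum creatinine. This is an inference from the document, whereas the reversed direction is plain on its face.

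**5. What still protects patients.** The operative test in item 15 is the investigator's judgment of clinical significance, and the parenthesis does not narrow it. A raised screening creatinine reaches the investigator and can lead to exclusion under item 15 or 18. Serious unstable renal disease falls under item 11. On study, chemistry is repeated at visits 4 and 6, clinically significant abnormalities are re-measured (section 8.2.4), the investigator may withdraw a subject (section 5.4), and treatment may be suspended for adverse events (section 6.5).

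**The case against.** The strongest reply is that this is a one-word slip in an illustrative parenthesis, in a text that reads as a translation, and that a competent investigator would see through it. Much of that stands. The rule that decides eligibility is intact, the relevant blood test is taken, and no route can be shown by which the phrase itself enrols a patient with impaired renal function. Whether sites worked from another language version without the slip cannot be checked here.

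A reader might infer more than the Protocol supports, in four ways.

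- **That the criterion admits patients with impaired renal function.** It does not. An example introduced by e.g. neither limits the exclusion nor makes anyone eligible.
- **That the lack of a clearance formula is a second defect.** It matters only if clearance was really intended. Once the item names serum creatinine, no formula is needed.
- **That the wording makes screening differ between sites.** Such variation comes mainly from the investigator-judgment clause, which also governs the thyroid example and item 18.
- **That the fixed dose leaves no remedy on study.** Section 6.5 bars dose changes but permits suspension for adverse events. The 50% figure comes from a single-dose study in healthy volunteers. The Protocol gives no exposure data in renal impairment from which to size a safety effect.

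What the reply does not remove is the error itself. It stands in an operative eligibility criterion, is repeated in the Abstract, and is not corrected by any of the safeguards, none of which supplies a renal limit in the right direction.

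**Conclusion.** The point holds as a minor wording error in a safety criterion. The only renal laboratory example in exclusion 15 is reversed and should be corrected. Its practical effect is limited to the guidance sites receive at screening, because investigator judgment, items 11 and 18 and the screening serum creatinine still allow exclusion. There is no statistical consequence for sample size, randomization, endpoint or analysis. The number of patients affected cannot be estimated from the document and may be none.

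The finding of reversed direction rests only on the fact that clearance falls as renal excretion worsens. The preferred replacement rests on the further inference that serum creatinine was intended.

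**What to change.** In section 5.2, item 15, and in the matching item of the Abstract, replace creatinine clearance with serum creatinine, so that the example reads as serum creatinine above the upper limit of normal. Leave the e.g. and the investigator-judgment clause as they are.

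The cost is one phrase in two places, carried in the next amendment. Serum creatinine is already part of the screening chemistry, so no new test, formula or visit procedure is needed.

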## Elimination criteria

For those subjects enrolled into this clinical study, they were removed from this trial if one of the following criteria is met:

(1) Subjects who did not meet the inclusion criteria or met the exclusion criteria;

(2) Subjects who did not have any medication records;

(3) Subjects with no records of efficacy and safety information after the baseline.

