### Analysis set of clinical trial

The analysis set defined for this study is as below:

1. Full analysis set (FAS)

It includes all the randomized subjects who were administrated at least 1 dose of double-blind study drug and had primary efficacy evaluation at baseline and at least one primary efficacy evaluation after the first dose of double-blind treatment. Unless otherwise specified, LOCF (last observation carried forward) will be used for the missing value imputation in the FAS.

FAS is the primary analysis data set for this trial.

1. Per protocol set (PPS)

It includes all the subjects who completed visit 6 and have no major protocol deviation.

1. Safety set (SS)

It includes all the subjects who were randomized and administrated at least one dose of the double-blind study drug. Subjects who were dispensed study drug but did not administrate any study drug will not included in SS.

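### Section 5.3 removes enrolled patients with an eligibility violation from the trial, while the FAS and safety set definitions keep them; nothing says which prevails

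*Protocol*

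**What the plan says.** Protocol section 5.3 (Elimination criteria) says of enrolled subjects that "they were removed from this trial if one of the following criteria is met". There are three criteria:

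- Criterion 1 is a breach of the entry criteria: "Subjects who did not meet the inclusion criteria or met the exclusion criteria".
- Criterion 2 is that no record of medication exists for the person.
- Criterion 3 is a lack of follow-up data: "Subjects with no records of efficacy and safety information after the baseline".

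Protocol section 11.2 (Analysis set of clinical trial) defines the FAS thus: "It includes all the randomized subjects who were administrated at least 1 dose of double-blind study drug". It adds the need for a primary efficacy evaluation at baseline and at least one after the first dose, and names the FAS as the primary set. For the safety set (SS) it says: "It includes all the subjects who were randomized and administrated at least one dose of the double-blind study drug". It leaves out only those who were given drug but took none. The per-protocol set (PPS) is the only set with a deviation condition: Visit 6 completed and no major deviation. None of the three definitions refers to section 5.3, and section 5.3 mentions no analysis set.

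**The concern.** A patient who is randomised, dosed and rated, and is later found to have violated an entry criterion, belongs in the FAS and the SS under one section and is out of the trial under the other. Both instructions cannot be followed.

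Two things are at stake. In the primary analysis, criterion 1 would take patients out after randomisation, at a time and by a process that section 5.3 does not fix. In the safety analysis it would take out patients who received the drug, together with any adverse events they had.

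**Working it through.** The plan gives no figure on this point, so there is none to reproduce. The check is a comparison of the rules.

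**Step 1. Does section 5.3 reach randomised, dosed patients?** Yes. Exclusion criterion 10 treats enrolment and randomisation as one event ("before randomization/enrollment"). Section 6.7 restricts study drug to enrolled subjects. Section 4.6 speaks of 260 enrolled cases and of their 1:1:1:1:1 randomisation.

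**Step 2. Apply each rule to the same randomised subject** (baseline HAM-D17 present in every row).

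| Subject | FAS (11.2) | SS (11.2) | Section 5.3 |
| --- | --- | --- | --- |
| Ineligible, dosed, post-dose HAM-D17 | in | in | removed, criterion 1 |
| Ineligible, dosed, no post-dose HAM-D17 | out | in | removed, criterion 1 |
| Eligible, dosed, neither efficacy nor safety record after baseline | out | in | removed, criterion 3 |
| Eligible, never dosed, no medication record | out | out | removed, criterion 2 |

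- Criterion 1 conflicts with the FAS (row 1) and with the SS (rows 1 and 2).
- Criterion 3 agrees with the FAS and conflicts with the SS only (row 3).
- Criterion 2 gives the same answer as the dose condition in both sets. The one gap is that a missing record does not prove that no dose was taken.

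**Step 3. Is criterion 1 confined to facts fixed before randomisation?** No. It covers anyone who met an exclusion criterion. Exclusion 5 includes failure to keep up contraception until 28 days after the last dose, which can be known only after treatment. Exclusion 15 turns on whether the investigator considers a finding clinically significant, and exclusion 18 on whether the investigator thinks the patient suitable. Section 5.3 sets neither a date for the decision nor a requirement that it be made blind.

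**Step 4. Size for criterion 1.** The protocol gives no rate of ineligible patients, so the rate is assumed at 2-5%:

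- 0.02 × 260 = 5.2 and 0.05 × 260 = 13, so about 5 to 13 patients in all.
- Per arm of 52: 0.02 × 52 = 1.04 and 0.05 × 52 = 2.6, so about 1 to 3 patients.

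**Step 5. Effect on the safety results.** Section 9.3 defines incidence as subjects with at least one adverse reaction divided by subjects evaluated for safety. Under criterion 1 a patient with an event leaves both the numerator and the denominator. Under criterion 3 a removed subject has no safety record after baseline, so no event recorded after baseline is lost and only the denominator shrinks. For illustration, one such subject in an arm of 52 multiplies that arm's incidence by 52/51 = 1.02.

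**The case against.** The best defence is that section 5.3 is not an analysis rule at all. It stands in the chapter on selecting subjects and names no analysis set. Section 11.2 is the specific provision, and a statistician working from it would keep ineligible dosed patients. On this view, removal means only that the patient stops taking part.

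That reading is just possible for criterion 1 but does not suit the section. Criteria 2 and 3 can be judged only in retrospect, from absent records. Stopping participation has its own section, 5.4, which already lists major protocol violations and asks for data to be obtained as far as possible. Section 5.3 has no such instruction. Even if it does mean stopping, it does not say that the patient stays in the FAS and SS.

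Four further points limit the finding, and they stand:

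- Eligibility is checked before randomisation (sections 4.7 and 7.2), so late violations should be few.
- The trial is double-blind and the first unblinding follows data lock (section 10), so most removals would be decided without knowledge of the arm. Blinding does not stop a removal from depending on response or tolerability, but it limits the bias.
- The FAS already has post-randomisation conditions (a dose and a later score). Section 5.3 would add to these exclusions and is not their only source.
- A subject with no record after baseline will often have no evidence of a first dose: drug is dispensed on Day 0, first taken on Day 1, and returned drug is first counted at Visit 3. Such a subject would mostly be outside the SS anyway.

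**Conclusion.** The contradiction is real for criterion 1 against both the FAS and the SS, and it leaves membership of the primary and safety sets undetermined. The text itself shows this. The size of 5 to 13 patients rests on the assumed 2-5%, and also on section 5.3 being applied in preference to section 11.2, which is the open question.

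A reader might go further and infer that the whole elimination rule contradicts both sets, that adverse events vanish under criterion 3, that the safety denominator falls substantially, or that the randomised comparison is broken. The documents do not support these. Criterion 2 largely matches the dose condition. On its natural reading criterion 3 needs both kinds of record to be absent, so no event recorded after baseline is lost. No figure is given for dosed subjects without records. Blinding until data lock tempers the bias.

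The analysis set definitions are themselves clear and the trial is exploratory, so this is a point that should be fixed rather than one that undermines the design.

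**What to change.** Add to section 5.3:

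- The analysis set definitions in section 11.2 alone govern membership of the FAS and the SS.
- An eligibility violation leads to exclusion from the PPS only, decided and documented before unblinding.
- Every randomised subject who took at least one dose of double-blind drug stays in the SS, including one with no record after baseline.

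Criterion 2 needs no separate rule for never-dosed subjects, because the SS definition already leaves them out.

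The cost is the wording of one protocol section. Sample size, visits and data collection do not change.
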